## 7.2 Justification for Inclusion/Exclusion Criteria

Provided below is a justification for criteria that are either not self-evident or differ in some way from standard practice in clinical trials in patients with MDD.

### 7.2.1 Outside Psychotherapy

Participants will only be eligible for study enrollment if they agree and are judged able, from a safety perspective, based on the opinion of a study psychiatrist, to suspend any ongoing outside psychotherapy for the duration of study involvement phase A (ie 42 days from dosing). The rationale for suspending outside therapy is to allow for adequate evaluation of the study intervention. Suspending outside psychotherapy for the duration of the study is similar to the need for participants not to be taking outside psychotropic medications (e.g. antidepressants) during the study period. As with continuing pre-existing antidepressant medications, allowing participants to continue pre-existing outside psychotherapy would potentially confound the ability to unambiguously interpret study findings regarding whether monotherapy with psilocybin delivered in a therapeutic context shows an antidepressant effect when compared to placebo. This is true for several reasons. First and foremost, continuance of outside psychotherapy would not be “per protocol” and hence would not be standardized, nor would it be randomized, leading to the possibility of it being unequally distributed across groups. Moreover, it is completely unknown whether outside psychotherapy would potentiate or diminish antidepressant responses to psilocybin. Starting with phase B, in the presence of clinically relevant MDD symptomatology, outside psychotherapy as well as antidepressant drug treatment may be introduced, as it is included in the exploratory outcome measures.

### 7.2.2 Benzodiazepines

Benzodiazepine medications for sleep and non-benzodiazepine sleeping medications will be allowed for participants who have been on a stable dose of such a medicine for at least 6 weeks prior to Screening. These medications are allowed because they have no psychotropic effects that might confound any potential differential antidepressant signal from the

psilocybin vs. niacin placebo. On the other hand, requiring discontinuation of these sleeping agents prior to study drug dosing would likely disrupt stable sleep patterns that were part of the pre-treatment depressive symptom profile, and by doing this might interfere with potential antidepressant signals from the study drugs. Because these agents are used at bedtime, they will be out of participants' systems prior to study drug dosing and thus should not interfere with either psychodynamic or pharmacokinetic properties of psilocybin.

### 7.2.3 Age range

The age range for the current study is typical for most antidepressant studies, with enrollment limited to individuals 20 years of age and older, but not older than 65 years. The rationale for excluding individuals with MDD younger than 20 is twofold. First, although not explicitly written in the current European Council Directive 2013/59/Euratom of 5 December 2013 (<https://eur-lex.europa.eu/eli/dir/2013/59/oj>), the Regional Radiation Safety Committee of Karolinska University Hospital Stockholm has hitherto recommended the age of included subjects to be 20 years or older. Second, younger subjects are at an increased risk of demonstrating a bipolar disease course with the passage of time and bipolar disease is believed to be contraindicated for the use of psilocybin. There are no data to support the use of psilocybin in patients with bipolar disorder, nor data on how likely psilocybin would be to induce a manic episode in patients with a bipolar diathesis. In addition to this particular concern regarding incipient or misdiagnosed bipolar disorder in those younger than 20, individuals in this age group are in general at increased risk for adverse psychological reactions to antidepressants.

This study will also exclude individuals older than 65 years of age. In addition, as with individuals younger than 20, older adults often differ from younger adults in factors associated with their depression and in their intervention response. For example, depression in older adults, especially when it is new onset, is significantly associated with the subsequent development of dementia. And studies suggest that older adults are less likely than younger adults to respond to pharmacological treatments for MDD when depression is associated with brain changes also associated with dementia.

Additionally, over the course of its long-term clinical development phase, over a thousand participants have received psilocybin under controlled conditions in clinical settings for various indications (including healthy control subjects), with subsequent results published in peer-reviewed journals. The modern-day trials, enrolling approximately 165 adult participants, include open-label, dose-escalating studies, as well as randomized, double-blind placebo-controlled trials, and enrolled both healthy volunteers and various subpopulations with differing indications. Multiple ongoing studies are continuing this exploration. All these studies had or currently have approval to enroll participants > 55 years (age ranges from 18-80 years). Furthermore, of the approximate 165 participants receiving study drugs in completed trials, 73 adult participants were > 55 years ([name]; [name]; [name]; [name], [name]; [name]; [name], *personal communication with RB*). To date, no Serious Adverse Events attributed to the study drug were reported for any participant in these trials, regardless of age.

For these reasons, selecting the 20-65 year age range maximizes the generalizability of any potential positive findings while reducing risk and constraining biological/phenomenological variance that might decrease the power to detect clinically-

relevant effects. Should results from the proposed study be promising, separate trials of psilocybin intervention in younger adult and geriatric populations would be warranted.

#### **7.2.4 Medically Healthy Participants**

The current study will enroll participants in good general overall medical health. While this somewhat limits the potential generalizability of any positive findings given the high comorbidity between mood disorders and medical disease, there are two primary reasons for choosing this strategy. First, medically-ill participants often have complex patterns of depressive pathogenesis born of the psychological stress of serious disease, but also likely from the direct physiological effects of the disease state itself, most notably the chronic immune activation that accompanies a wide range of medical illnesses. Given this, separate studies are indicated to examine the potential antidepressant effects of psilocybin in patients with MDD and significant medical comorbidity.

#### **7.2.5 Psychiatric Symptoms**

Study inclusion/exclusion criteria include several exclusions related to psychiatric symptoms and conditions. Participants with active suicidal ideation with intent to act are excluded because these individuals require immediate psychiatric intervention with currently approved therapeutic modalities. The safe study of such individuals would require an inpatient setting and the current study will be conducted on an out-patient basis. Similarly, individuals with a history of medically significant suicide attempt will be excluded given evidence that a recent history of suicide attempts increases the short-term risk for subsequent suicide attempts.

Individuals who are experiencing depression in the context of conditions characterized by a heightened risk for psychotic features, including schizophrenia and bipolar I and II disorder, are also excluded, including individuals with first-degree relatives with these conditions. These exclusions are based on the fact that not enough is known regarding the risks of a psychedelic experience in individuals with a vulnerability to psychosis to justify their inclusion in the current study. At the least, such individuals might have experiences occasioned by psilocybin that would differ markedly in their character and effects from experiences that would be more typical for individuals without psychosis risk.

As is common practice in phase 2 studies of new antidepressant modalities, individuals with active drug/alcohol abuse are excluded, as are those who have only recently achieved sobriety. Justification for these exclusions comes from evidence that antidepressant treatments are less effective in those who are actively abusing drugs/alcohol and from the fact that relapse rates are high during early sobriety, increasing the risk of a return to substance use during the study.

Because psilocybin administered under the SaS requires the development of rapport between participant and his/her intervention Facilitators, participants will be excluded prior to intervention if it is judged by the Facilitators (with agreement from a study clinician) that a given participant is not demonstrating a minimal degree of involvement/engagement with the intervention team.

Also, because this study focuses on MDD, participants with comorbid psychiatric conditions (e.g., obsessive-compulsive disorder, panic disorder, ADHD, Borderline Personality Disorder) that are judged at Screening to be a more significant source of distress/impairment than the MDD will be excluded from study participation. Comorbid psychiatric disorders other than those specifically disallowed (i.e. psychotic disorders, bipolar I and II disorder,

antisocial personality disorder) will be allowed if it is determined based on assessment at Screening that the participant's primary condition is MDD.

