22. Have a first-degree relative with schizophrenia spectrum or other psychotic disorders (except substance/medication-induced or due to another medical condition), or Bipolar I Disorder
23. Have a psychiatric condition judged to be incompatible with establishment of rapport with the Facilitators or safe exposure to psilocybin
24. Report the following suicidal ideation or suicidal thoughts defined as:
  - a. Have a score of  $\geq 5$  on Item 10 (suicidal thoughts) of the central-rater or computer administered MADRS at Screening or Baseline; or
  - b. Have any suicidal ideation or thoughts, in the opinion of the study physician or PI, that presents a serious risk of suicidal or self-injurious behavior at any time prior to randomization
25. Have any suicidal ideation or thoughts, in the opinion of the study physician or PI, that presents a serious risk of suicidal or self-injurious behavior
26. Have any physical or psychological symptom, medication or other relevant finding at Screening or Baseline, based on the clinical judgment of clinical/medical study personnel, that would make a participant unsuitable for the study.
27. Have an allergy or intolerance to any of the materials contained in either drug product
28. Have one or more pathological blood test results as defined in 5.6.3 (as determined by a study physician).

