  - b. Baseline blood pressure SBP >140 mmHg or DBP > 90 mmHg on three separate readings
10. Have a history of stroke or Transient Ischemic Attack (TIA)
11. Have moderate to severe hepatic impairment, as indexed by a Child-Pugh score  $\geq 7$
12. Have epilepsy
13. Have insulin-dependent diabetes
  - o Note: Participants who are taking oral hypoglycemic agent and have a history of hypoglycemia requiring medical intervention will be excluded
14. Are unable or unwilling to adhere to the following medication requirements:
  - a. Agree to suspend sildenafil (Viagra®), tadalafil, or similar medications at least 72 hours prior to dosing
  - b. If taking any supplement containing >20 mg of niacin, agrees to suspend use for the duration of the study
15. Have a positive urine drug test including Amphetamines, Barbiturates, Buprenorphine, Benzodiazepines, Cocaine, Cannabis, Methamphetamine, MDMA, Methadone, Opiates (Morphine, Oxycodone), Phencyclidine (PCP), and Tetrahydrocannabinol (THC). Exceptions are made for prescribed Benzodiazepines (stable dose for sleep or anxiety).
  - o Note: Benzodiazepine medications for sleep and non-benzodiazepine sleeping medications will be allowed to continue through the study period for participants who have been on a stable dose of such a medicine for at least 6 weeks prior to Screening, as determined during review of concomitant medications
  - o Note: Participants using cannabis, including legal cannabis, for any purposes will be excluded
  - o Note: Participants who are taking prescription maintenance methadone or buprenorphine naloxone will be excluded
  - o Note: Prescription opiates must have been stopped at least 5x the elimination half-life of the specific drug at the time of inclusion, as confirmed with a negative urine drug screen.
16. Nicotine dependence that would disallow an individual to be nicotine free for the 7-10 hours during the dosing period
17. Meet ICD-10 criteria for schizophrenia spectrum or other psychotic disorders, including MDD with psychotic features (except substance/medication-induced or due to another medical condition), or Bipolar I Disorder, Bipolar II Disorder and bipolar disorder NOS.
  - o Note: Participants with any lifetime diagnosis of schizophrenia spectrum or other psychotic disorders will be excluded
18. Meet ICD-10 criteria for antisocial personality disorder
19. Meet ICD-10 criteria for a moderate or severe alcohol or drug use disorder (excluding caffeine)

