  - o Note: Participants with a diagnosis of alcohol or drug use disorder within the past 12 months will be excluded
20. Have presence of any psychiatric condition or symptom judged by the PI (or designee) to be a more significant clinical problem than MDD for the participant.
21. Have a first-degree relative with schizophrenia spectrum or other psychotic disorders (except substance/medication-induced or due to another medical condition), or Bipolar I Disorder

22. Have a psychiatric condition judged to be incompatible with establishment of rapport with the Facilitators or safe exposure to psilocybin
23. Report the following suicidal ideation or suicidal thoughts defined as:
  - a. Have a score of  $\geq 5$  on Item 10 (suicidal thoughts) of the central-rater or computer administered MADRS at Screening or Baseline; or
  - b. Have any suicidal ideation or thoughts, in the opinion of the study physician or PI, that presents a serious risk of suicidal or self-injurious behavior at any time prior to randomization
24. Have any suicidal ideation or thoughts, in the opinion of the study physician or PI, that presents a serious risk of suicidal or self-injurious behavior
25. Have any physical or psychological symptom, medication or other relevant finding at Screening or Baseline, based on the clinical judgment of clinical/medical study personnel, that would make a participant unsuitable for the study.
26. Have an allergy or intolerance to any of the materials contained in either drug product
27. Have Hepatitis B, C or HIV
28. Have one or more pathological blood test results as defined in 5.6.3 (as determined by a study physician; with the exception of CRP).

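### Section 7.2.5 excludes people with a past medically significant suicide attempt or a first-degree relative with bipolar II, but neither numbered exclusion list does; separately and of less weight, inclusion 7 is worded two ways

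*Protocol*

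**What the plan says.** **Suicide attempt.** Section 7.2 introduces itself this way: "Provided below is a justification for criteria that are either not self-evident or differ in some way from standard practice". Under it, 7.2.5 states that "individuals with a history of medically significant suicide attempt will be excluded". The reason given is that "a recent history of suicide attempts increases the short-term risk for subsequent suicide attempts".

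**Relatives.** Section 7.2.5 goes on to people whose depression occurs with conditions carrying a raised risk of psychosis, "including schizophrenia and bipolar I and II disorder, are also excluded, including individuals with first-degree relatives with these conditions". Its reason is that too little is known about what a psychedelic experience does to someone vulnerable to psychosis.

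**The numbered lists.** The suicidality exclusions are items 24–25 in the synopsis and 23–24 in 7.1.2. They open with "Report the following suicidal ideation or suicidal thoughts defined as" and continue with "Have any suicidal ideation or thoughts, in the opinion of the study physician or PI, that presents a serious risk". The family-history exclusion (synopsis item 22, 7.1.2 item 21) ends with "or due to another medical condition), or Bipolar I Disorder".

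**Inclusion 7.** Both versions require a Screening MADRS of at least 22 and limit the improvement since web screening. The synopsis allows at most 30% *or* at most 7 points; 7.1.1 allows at most 30% *and* at most 7 points. The Study Description and Overview in the synopsis, and section 6.1, give the 30% limit with no 7-point limit beside it.

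**The concern.** The numbered lists define who may and may not be randomized. A justification section should explain criteria that exist, yet 7.2.5 explains two that do not. Staff who follow the lists exactly could dose people whom the sponsor describes as excluded for their own safety. The setting adds weight. The study is outpatient, and section 17.1.4 says participants forgo established treatment and that worsening, including suicidal ideation, may be likelier on niacin. Anyone who reads 7.2.5 to judge the protection offered would believe these groups are kept out.

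For inclusion 7, two readers of one protocol can reach opposite decisions on the same patient, and whether an enrolment counts as an eligibility deviation would depend on the page used.

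**Working it through.** The first two checks are comparisons of text. The third is an enumeration. The plan gives no figure of its own on these points to reproduce.

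**1. Attempt history**

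| Place | Past attempt | Ideation |
|---|---|---|
| 7.2.5 | excludes | active ideation with intent excludes |
| Synopsis items 24–25 | not mentioned | MADRS item 10 of 5 or more, or clinician-judged serious risk |
| 7.1.2 items 23–24 | not mentioned | same |

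The ideation score cannot stand in for history, because section 5.5.1 says MADRS items rate the prior week. A patient with a serious attempt in the past and no current ideation meets neither limb of the suicidality items.

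**2. First-degree relatives**

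| Place | Psychotic disorder | Bipolar I | Bipolar II |
|---|---|---|---|
| 7.2.5 | excludes | excludes | excludes |
| Synopsis item 22 | excludes | excludes | not mentioned |
| 7.1.2 item 21 | excludes | excludes | not mentioned |

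Bipolar I is not shorthand for both types here. For the participant's own diagnosis, 7.1.2 item 17 spells out "or Bipolar I Disorder, Bipolar II Disorder and bipolar disorder NOS", and synopsis item 18 does the same.

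**3. Inclusion 7**

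Inputs:
- W is the modelled web score, MADRS-S + 3. Web entry needs MADRS-S of at least 19, so W starts at 22. MADRS-S has 9 items scored 0–6, so its maximum is 54 and W ends at 57.
- S is the Screening MADRS, 22 to 60.
- The drop is D = W − S.

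Rules:
- *or*: D ≤ the larger of 0.30W and 7
- *and*: D ≤ the smaller of 0.30W and 7

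Because 0.30W exceeds 7 once W is above 7/0.30 = 23.3, from W = 24 *or* means 30% and *and* means 7 points. At W = 22 and 23 the floor S ≥ 22 permits drops of at most 0 and 1, so no rule binds. At W = 24 to 29 the floor permits drops of at most 2 to 7, and both rules admit them all. The rules first part at W = 30, where the floor permits a drop of 8: this is within 0.30 × 30 = 9 but above 7.

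| W (raw MADRS-S) | Lowest S, *or* | Lowest S, *and* | Lowest S, 30% alone | Disputed S |
|---|---|---|---|---|
| 29 (26) | 22 | 22 | 22 | none |
| 30 (27) | 22 | 23 | 22 | 22 |
| 33 (30) | 24 | 26 | 24 | 24–25 |
| 36 (33) | 26 | 29 | 26 | 26–28 |
| 40 (37) | 28 | 33 | 28 | 28–32 |
| 50 (47) | 35 | 43 | 35 | 35–42 |
| 57 (54) | 40 | 50 | 40 | 40–49 |

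Over all integer pairs, 1154 are eligible under *or* and 998 under *and*, so 1154 − 998 = 156 are disputed. They occur at every W from 30 to 57, which is 28 of the 36 values. *Or* and 30% alone never differ. The synopsis criterion, the synopsis overview and section 6.1 therefore give the same improvement limit, and 7.1.1 is the outlier.

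**The case against.** On the first two points, the two numbered lists agree with each other and 7.1.2 says ineligibility follows from its items. Section 7.2 is rationale, and section 4.1 says the protocol is partly based on another sponsor's. The stray text could therefore be in 7.2.5, with no criterion missing. That stands as a possibility, and it is why correcting 7.2.5 is an acceptable repair. It does not remove the contradiction, since 7.2.5 says these people are excluded, not that they may be.

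Clinician judgement is the next defence. Items 22–25 of 7.1.2 cover conditions incompatible with safe exposure, serious suicidal risk and any finding that makes someone unsuitable; 8.5.1 and 9.1.1 add checks up to dosing. Once such a judgement is made, exclusion is mandatory. But the judgement itself is left open, and items 23b and 24 turn on ideation. These items are narrower than a categorical rule on history or family. Suicidality monitoring and the option of antidepressant treatment (sections 5.5.1, 17.1.4 and 18.1.3) act after entry.

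A reader might infer that attempt history will go unasked, because section 5.6.1 does not name it among the MINI's contents. The documents do not support that: the list there is not stated to be exhaustive, and a screening psychiatric interview is scheduled in Table 1.

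On inclusion 7, a reader might see an even split, or take the 7-point cap as the better fit to the aim of avoiding spontaneous remission. Neither is supported. The overview gives that aim as the reason for the 30% limit. A fixed cap also tightens with severity: at W = 50, 7 points is a 14% drop. And because W is a self-rating plus a constant, a gap between self-rater and clinician could count as improvement. It is true that the overview and 6.1 can be read as necessary conditions only, so they favour the 30% reading without proving it.

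**Conclusion.** The contradiction between 7.2.5 and both numbered lists holds for attempt history and for relatives with bipolar II. It should be fixed, chiefly because of the attempt history. Under the lists as written, a patient with a past serious attempt and no current ideation, or with a bipolar II parent, can be randomized. The size in patients is unknown, because the documents give no frequency for either group.

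The inclusion 7 discrepancy is real but lesser. It changes eligibility at every modelled web score from 30 up, and 7.1.1 is the line out of step. The 156 disputed score pairs weight all integers equally up to the scale maximum; they are not patient counts.

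A reader might go further and infer that the trial's power or its treatment comparison is compromised. Nothing here supports that: eligibility is settled before randomization and applies alike to both arms, and no sample-size input is involved. Nor do the documents show that anyone has been or will be wrongly dosed, only that the lists would allow it.

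The conclusion assumes that staff screen from the numbered lists, as the wording of 7.1 implies.

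**What to change.** 1. Add a past medically significant suicide attempt as a numbered exclusion in the synopsis and in 7.1.2, asked at the screening psychiatric interview already in Table 1. The sponsor should state whether it is lifetime or within a recent window, since 7.2.5 excludes on history but argues from recent attempts.
2. Add bipolar II to the first-degree-relative exclusion (synopsis item 22, 7.1.2 item 21).
3. If either exclusion is not intended, correct 7.2.5 instead.
4. State one improvement rule identically in the synopsis and 7.1.1. The simplest course is 30% alone. If the sponsor does want the 7-point cap, it should be written into the synopsis overview, synopsis inclusion 7 and section 6.1 as well.

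The cost is amendment wording and a matching eligibility form, with no new visit or assessment. The downside is an unknown, probably small, number of additional screen failures, larger if the attempt exclusion is lifetime or the 7-point cap is kept.
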